### Analyses

Mixed models with intention-to-treat will be used to explore the efficacy of EMDR in reducing symptoms of PD. These analyses will be used for the majority of other outcome measures. The cost-effectiveness evaluation will be undertaken according to the Dutch guidelines for cost effectiveness studies taken a societal perspective [34]. The severity of PD (ADP-IV) will be used for effectiveness. The TiC-P is used to collect data on the utilization of medical services and productivity loss. Utility scores are estimated using the EQ-5D-5L and MHQoL will measure the effects. A cost-utility analysis and a cost-effectiveness analysis (CEA) are conducted. The cost-utility is calculated as the incremental costs and utilities, which yields a cost per QALY estimate. The cost-effectiveness is expressed in the incremental costs and scores on the ADP-IV.

Multilevel modelling is used to model cost-effectiveness. For assessing the uncertainty, cost-effectiveness acceptability curves and cost-effectiveness planes will be created after bootstrapping. The acceptability curve illustrates the probability that the cost-effectiveness ratio will be accepted for different thresholds. In a cost-effectiveness plane, both incremental costs and incremental effects are plotted to account for combinations. Sensitivity analyses will be performed after the analysis if necessary.

Subgroup analyses will be performed to further investigate the effectiveness of EMDR therapy in patients with or without PTSD or with BPD or any other PD.

Recordings will be made of the qualitative interviews. All transcripts will be summarized by the researchers and provided to participants for respondent validation. The researchers will thoroughly read all transcripts, highlight all potentially relevant excerpts and sort them based on the research questions. These sorted data will then be independently coded by the researchers; excerpts will be grouped based on their similarities. Then, these groupings will be identified/themed. Consequently, the researchers will confer and attempt to reach a consensus on all groupings and themes, resulting in a preliminary codebook. The codebook and two information-rich transcripts as examples will be presented to the study group. Themes will be reviewed, focussing on understanding the data and confirming that the data still correspond to the assigned themes. These themes will form the basis of the conclusions of this sub-study and will be reported.

Predictors of treatment success and discontinuation will be separately assessed with logistic regression analyses and calculated with 5000 bootstraps. Treatment success is defined as a loss of PD diagnosis at T1 in a first analysis, and at T12 in a second analysis. Considering the literature (see introduction [5]) and to test whether effectiveness differs between specific PDs, patients with or without PTSD, the centres of treatment and the EMDR therapists, the following predictors will be entered into a backward logistic regression with a two-tailed significance level of *α* = .05 as criterion: (1) pre-treatment symptom severity, (2) patient-rated therapeutic alliance, (3) specific PS diagnosis, (4) PTSD diagnosis, (5) centre of treatment and (6) EMDR therapist. Considering the literature (see introduction [50, 61]) and to test whether discontinuation differs between specific PDs, patients with or without PTSD, the centres of treatment and the EMDR therapists, the following potential predictors of treatment discontinuation will be entered into a backward logistic regression with a two-tailed significance level of *α* = .05 as criterion: (1) treatment credibility, (2) age, (3) education, (4) occupational levels, (5) amount of PD diagnoses, (6) amount of PD criteria, (7) general functioning, (8) substance use, (9) severity of adverse childhood events, (10) specific PS diagnosis, (11) PTSD diagnosis, (12) centre of treatment and (13) EMDR therapist. Analyses will be checked for robustness by redoing them with survival analysis.

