## Method

### Design

The TEMPO study is a single-blind randomized controlled superiority trial with two arms, i.e. EMDR therapy and waiting list. The trajectory of a participant through the study is shown in Fig. 1. The experimental group will receive ten bi-weekly EMDR sessions of 90 min each, with a total duration of 15 h of treatment over 5 weeks. The groups are compared at baseline (pre-randomization; T0), post-intervention (after 5 weeks; T1), 3-month (T3), 6-month (T6) and 12-month (T12) follow-up. At baseline, demographical data will be collected for predictive analyses of treatment success and treatment dropout. At T1, patient dropout will be recorded and a random selection of patients in the experimental condition will be interviewed to assess their experiences with EMDR therapy. Until T3, patients do not receive further treatment, except in a crisis situation. At T3, all patients will be invited by their therapist for a consultation to examine whether (further) treatment is necessary. Any available treatment, except EMDR therapy, will be offered. At T12, when participation is concluded, control patients will also be offered the opportunity to receive EMDR therapy.

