#### Waiting list

The other half of the participants will be allocated to the control condition, namely a waiting list. They will not receive EMDR therapy and any other treatment for their PD is postponed until after T3 as well. They will be informed of their condition right away and invited for another appointment for post-intervention measurements (T1). Three months later, besides T3 assessments, all participants will confer with the therapist who did the diagnostic procedure on admission, to decide which treatment is most suitable. Patients will be offered the opportunity of following any available treatment, but not EMDR therapy, for their PD. The patient will be registered for the chosen treatment based on the date of intake so that the patient does not have additional waiting time. At study termination (T12), participants in the control condition will also be offered EMDR therapy.

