***Waiting list***								
**Assessments:**								
***ADP-IV***		x			x	x	x	x
***CAPS-5***^**a**^		x			x	x	x	x
***SCID-5-P***^**a**^	x				x	x	x	x
***TiC-P***		x			x	x	x	x
***EQ-5D-3L***		x			x	x	x	x
***MHQoL***		x			x	x	x	x
***LEC-5***		x						
***PCL-5***		x			x	x	x	x
***CTQ-SF***		x						
***DERS***		x			x	x	x	x
***BSPC***		x			x	x	x	x
***LPFS-BF 2.0***		x			x	x	x	x
***OQ-45***		x			x	x	x	x
***Appendix A/B***^**a**^					x^b^			

*EMDR* Eye Movement Desensitization and Reprocessing, *ADP-IV* Assessment of DSM-4 Personality Disorders, *CAPS-5* Clinician-Administered PTSD scale for DSM-5, *SCID-5-P* Structured Clinical Interview for DSM-5 Personality Disorders, *TiC-P* Treatment Inventory of Costs in Patients with psychiatric disorders, *EQ-5D-3L* EuroQol—5 dimensions—3 levels, *MHQoL* Mental Health Quality of Life, *LEC-5* Life Events Checklist for the DSM-5, *PCL-5* PTSD Checklist for DSM-5, *CTQ-SF* Childhood Trauma Questionnaire—Short form, *DERS* Difficulties in Emotion Regulation Scale, *BSPC* Brief State Paranoia Checklist, *LPFS-BF 2.0* Level of Personality Functioning Scale—Brief Form 2.0, *OQ-45* Outcome Questionnaire-45

^a^Interview

^b^Experimental condition only

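### The regression meant to show where EMDR is more or less effective has no treatment comparison in it, so it identifies who remits, not who gains from EMDR

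*Protocol article*

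**What the plan says.** All of the following is in the protocol article.

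- **Purpose.** Analyses gives the aim of the treatment-success regression as "to test whether effectiveness differs between specific PDs, patients with or without PTSD, the centres of treatment and the EMDR therapists".
- **Outcome.** "Treatment success is defined as a loss of PD diagnosis at T1 in a first analysis, and at T12 in a second analysis".
- **Predictors.** Pre-treatment symptom severity comes first; the others are "2) patient-rated therapeutic alliance, (3) specific PS diagnosis, (4) PTSD diagnosis, (5) centre of treatment and (6) EMDR therapist". They enter a backward logistic regression at a two-tailed 0.05 criterion. Allocation is not listed, nor is any product of allocation with a predictor. The analysis population is not named.
- **Control arm.** Under Waiting list: "They will not receive EMDR therapy and any other treatment for their PD is postponed until after T3 as well". The Introduction gives spontaneous recovery as the reason for having an untreated comparator.
- **After T3.** Under Design: "Any available treatment, except EMDR therapy, will be offered".
- **Data available.** Table 1 schedules the SCID-5-P and ADP-IV at T1, T3, T6 and T12. Only the experiences interview is marked as limited to the experimental condition.
- **Subgroups.** Analyses also states: "Subgroup analyses will be performed to further investigate the effectiveness of EMDR therapy in patients with or without PTSD". The same sentence plans a second split, BPD against the remaining PDs. It does not say how these analyses will be done.

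**The concern.** A difference in effectiveness between patient groups is a difference between two EMDR-versus-waiting-list contrasts. The regression contains no such contrast. Its outcome is a level (diagnosis lost or not), and a significant PTSD, PD-type or centre coefficient says only that one group loses the diagnosis more often than another. The same gap could exist on the waiting list.

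At stake are the statements the trial will make about who benefits from EMDR. If these are read from this model, natural course and treatment benefit cannot be told apart, although the trial has a randomised arm that can separate them. In the T12 version the outcome also carries the effect of whatever other treatment was received after T3.

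**Working it through.** The article states no figure for this analysis, so there is none to reproduce. The check has two parts: what the listed model can estimate, and how far that can lie from a difference in effectiveness.

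**1. What the model can estimate.** EMDR therapist has no value for a waiting-list patient, and in practice neither does therapeutic alliance. With these predictors the model can be fitted only in the EMDR arm. This is an inference, since no population is named. It is not decisive: if both arms were pooled, the listed model would still have no term for a difference in treatment effect.

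**2. How the two quantities relate.** Write odds(p) = p/(1 − p), and take PTSD as the factor.

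- EMDR-arm OR = odds(EMDR, PTSD) / odds(EMDR, no PTSD). This is what the regression estimates.
- Ratio of treatment ORs = [odds(EMDR, PTSD)/odds(WL, PTSD)] / [odds(EMDR, no PTSD)/odds(WL, no PTSD)]. This is effect modification on the logit scale.
- Hence EMDR-arm OR = ratio of treatment ORs × control-arm OR, where control-arm OR = odds(WL, PTSD)/odds(WL, no PTSD).

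The two agree only when the control-arm OR is 1.

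**3. Numbers.** The article gives no remission rates, so every rate below is an assumption. WL = waiting list; odds ratios compare PTSD with no PTSD; risk differences (RD) and treatment ORs are given as PTSD / no PTSD.

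| Case | PTSD: WL, EMDR | No PTSD: WL, EMDR | Control-arm OR | EMDR-arm OR | RD (points) | Treatment ORs | Ratio of treatment ORs |
|---|---|---|---|---|---|---|---|
| 1 | 5%, 25% | 20%, 40% | 0.21 | 0.50 | 20 / 20 | 6.33 / 2.67 | 2.38 |
| 2 | 10%, 30% | 30%, 50% | 0.26 | 0.43 | 20 / 20 | 3.86 / 2.33 | 1.65 |
| 3 | 10%, 25% | 25%, 50% | 0.33 | 0.33 | 15 / 25 | 3.00 / 3.00 | 1.00 |
| 4 | 10%, 40% | 30%, 40% | 0.26 | 1.00 | 30 / 10 | 6.00 / 1.56 | 3.86 |
| 5 | 10%, 35% | 35%, 50% | 0.21 | 0.54 | 25 / 15 | 4.85 / 1.86 | 2.61 |
| 6 | 10%, 15% | 10%, 40% | 1.00 | 0.26 | 5 / 30 | 1.59 / 6.00 | 0.26 |

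Case 5 in full: EMDR-arm OR = (0.35/0.65)/(0.50/0.50) = 0.54. Treatment ORs are (0.35/0.65)/(0.10/0.90) = 4.85 and (0.50/0.50)/(0.35/0.65) = 1.86, and 4.85/1.86 = 2.61.

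- Cases 1 and 2: the regression shows a difference although the risk differences are equal.
- Case 3: it shows a difference although the treatment ORs are equal.
- Case 4: it shows nothing although the effects differ on both scales.
- Case 5: it points the opposite way on both scales.
- Case 6: it agrees, because control remission is equal.

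**4. At the trial's size.** In 20,000 simulated trials of 159 patients under case 5, with half having PTSD, the EMDR-arm estimate had PTSD patients doing worse in 91%. The two-arm risk-difference contrast had them gaining more in 75%. These are directions of estimates, not significant results.

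**5. Power of the two-arm test.** Under case 5 with 40 patients per cell, the log ratio of treatment ORs is 0.96. Its standard error is √(1/(40·0.10·0.90) + 2/(40·0.35·0.65) + 1/(40·0.50·0.50)) = √0.598 = 0.77. The power at two-sided 0.05 is about 24%.

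**The case against.** The strongest reply is that the control arm is used elsewhere for this question. Analyses plans subgroup analyses of effectiveness by PTSD and by BPD versus other PD, in a trial whose effectiveness aim is EMDR against waiting list. They can naturally be read as between-arm contrasts. This stands in part. A reader might infer that the plan throws the control group away when asking who benefits, and the article does not support that. But no interaction test is stated for the subgroups, centre and PD types other than BPD are not covered, and the purpose given to the regression remains.

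Second, the regression belongs to an aim about predictors of success, for which a within-arm model is legitimate. That also stands: the model may stay, and only the purpose attached to it is wrong. Nor is this detail awaiting an analysis plan, because the article itself fixes purpose, outcome, predictors and selection rule, and they do not match.

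Third, the rates are assumed, and a large gap in untreated loss of diagnosis after five weeks is not shown. This is correct. A reader might infer that the regression will give the wrong answer. The article supports only that it can, and that the model alone cannot reveal whether it has.

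Fourth, the Discussion already lists varying treatment after T3 as a weakness and says healthcare use is recorded. It does not connect this with the T12 predictor model.

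**Conclusion.** The point holds as a mismatch between a stated purpose and the model meant to serve it. As written, the regression identifies who loses the diagnosis, not for whom EMDR does better than waiting list. For PTSD, PD type and centre, its coefficients equal differences in effectiveness (on the odds-ratio scale) only if waiting-list remission is equal across the groups. Where it is not, the assumed cases show EMDR-arm odds ratios of 0.33 to 0.54 with no difference or an opposite one on at least one scale, and 1.00 with a real difference. The size in this trial cannot be known from the article.

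The conclusion rests on the predictor list being complete as printed. The restriction to EMDR patients is inferred, but the conclusion survives without it. Therapist is a different matter: differences between therapists can be described only within the EMDR arm. The primary comparison and the sample size are unaffected.

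**What to change.** 1. Describe the treatment-success regression as prognostic among EMDR-treated patients, and drop the claim that it tests differences in effectiveness by PTSD, PD type or centre. Keep therapist as a description within the EMDR arm.
2. In all randomised patients, add allocation-by-PTSD, allocation-by-BPD and allocation-by-centre interactions to the mixed model, evaluated at T1, before other PD treatment is offered. Report each estimate with its confidence interval and label it exploratory.
3. State that predictor results at T12 also reflect treatment received after T3.

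**Cost.** A few model terms and a change of wording; the outcome data are already scheduled in both arms. The interactions will have low power (about 24% in the binary case worked above; the mixed-model figure will differ), so they will seldom settle who benefits. The mixed model answers for symptom severity at T1. It does not answer for loss of diagnosis, nor for T12.

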## Discussion

The present study, entitled the Trauma-focused EMDR for Personality disorders among Outpatients (TEMPO) study, is the first single-blind randomized controlled superiority trial that primarily investigates the effectiveness of EMDR therapy on personality disorder (PD) severity in a large sample of PD patients with a follow-up period of 1 year. Based on previous research findings, it is hypothesized that the data of the TEMPO-study will support EMDR therapy as being both an effective and cost-effective treatment for PD. Treatment with EMDR therapy is expected to be associated with a significant reduction in symptoms of PD, a significant decrease in proportion of patients no longer fulfilling the diagnostic criteria of a PD, and an increase in personal functioning, quality of life, and mental health outcomes, evidently favouring the patient. Furthermore, it is hypothesized that the duration of further treatment after EMDR therapy, treatment waiting time and treatment cost will be reduced, favouring the patient group and society at large.

This study has a number of strengths. Firstly, it is a multicentre, outpatient trial that includes a wide variety of PD patients and EMDR therapists, enhancing the external validity of the study. Secondly, a broad range of outcome measures is used in addition to measures of PD symptomatology, such as measures involving cost-effectiveness, and severity of trauma symptoms, which is likely to extend the literature on the effectiveness of EMDR therapy for (sub-threshold) PTSD in comorbid PTSD and PD populations, functioning, quality of life and patients’ experiences with EMDR therapy. Thirdly, the study includes multiple follow-up measurements, documenting the longevity of the hypothesized effects. Fourthly, treatment protocol adherence by EMDR therapists will be evaluated utilising a stopwatch and video recordings. These types of measures can help therapists to stay focused, not to elaborate, and to encourage sticking to the protocol. In addition, it will be possible not only to count the number of sessions, but also to calculate the average therapy time, and of course to determine afterwards to what extent the protocol was applied correctly. Also, some weaknesses of the study should be noted that cannot be avoided for ethical reasons. Firstly, blinding participants in the experimental condition is impossible and participants in the control condition should be informed of their allocation. Expectancy-effects might therefore influence the results. However, at all times, assessing researchers are blinded to the condition the participant is in. Secondly, after three months of follow-up, patients will be offered further treatment. The type of treatment, and therefore the intensity and duration of the treatments, may vary substantially among participants. However, the measurements used for the cost-effectiveness analyses include measures of healthcare consumption, allowing collection of exact data on the interventions that patients receive after T3. With these data, differences in health care utility between the control and experimental group can be explored.

In conclusion, the present study is the first RCT that will determine the effectiveness of EMDR therapy in reducing PD symptom severity and its ability to make patients no longer meet the diagnostics criteria of their PD at 1-year follow-up. If EMDR therapy indeed proves to be (cost-)effective in reducing or abolishing PD symptoms, this would provide a strong argument for including EMDR therapy as a standard treatment option for PDs, thereby significantly reducing treatment duration and costs, evidently benefiting the individual and society at large.

Protocol version 2, 29-11-2021

## Trial status

Inclusion: started 15 February 2021, approximate ending 15 August 2023

## Appendix A: Interview experiences with EMDR

*VOOR DE ONDERZOEKER: We willen inzicht krijgen in de ervaringen van patiënten met EMDR-therapie. De volgende (deels overlappende) vragen kunnen daarbij gesteld worden. De onderzoeker kan vervolgens doorvragen om additionele informatie te vergaren. Het einddoel is om duidelijk te maken hoe de patiënt zijn of haar behandeling met EMDR heeft ervaren.*

1. Hoe kijkt u terug op uw EMDR-behandeling?
2. Vindt u dat uw EMDR-behandeling succesvol is geweest? Waar merkt u dat aan? Welke specifieke klachten zijn verminder of verdwenen?
3. In hoeverre verschilt uw leven van voor en van na de EMDR-behandeling?
4. Had de EMDR-behandeling voor u ook nadelen? Wat was concreet het nadeel?
5. Specifiek, in hoeverre merkte u bijeffecten van de EMDR kort na een sessie?
6. Vond u de voordelen van de behandeling opwegen tegen de nadelen?
7. Heeft de EMDR-behandeling ook een (positief of negatief) effect gehad op uw andere behandelingen? Heeft u ervaringen uit de EMDR-behandeling nader besproken in uw hoofdbehandeling?
8. Wat vond u van het moment waarop u EMDR-behandeling heeft gevolgd? Zou EMDR eerder of later in het proces moeten worden gegeven?
9. Wat vond u van uw EMDR-behandelaar? Wat hielp u en wat niet?
10. Hoe zou u, op een schaal van 1 (verschrikkelijk) tot 10 (uitstekend), de therapeutische band met uw behandelaar beoordelen?
11. Bent u tevreden over de keuze om destijds een EMDR-behandeling te gaan starten? Zou u dezelfde keuze nog eens maken?
12. Zou u het anderen (met dezelfde klachten) aanraden ook een EMDR-behandeling te volgen? Waarom?
13. Heeft u nog verbeteringen voor onze EMDR-behandeling?

## Appendix B: English translation of interview experiences with EMDR

*FOR THE RESEARCHER: We would like to gain insight in patients’ experiences with EMDR therapy. The following (partly overlapping) questions could be used in this regard. The researcher can subsequently dig deeper to retrieve additional information. The end goal is to elucidate how the patient experienced his or her treatment with EMDR.*

1. How do you look back on your treatment with EMDR?
2. Do you think your EMDR treatment was successful? What makes you think that? Which specific complaints have diminished or disappeared?
3. To what degree does your life before differ from your life after EMDR treatment?
4. Were there any cons of your treatment with EMDR? Concretely, what cons did you experience?
5. To what degree did you notice side-effects of EMDR treatment shortly after a session?
6. Did the pros outweigh the cons?
7. If applicable, did the EMDR treatment also have an effect (positive or negative) on other treatments? Did you discuss your experiences with EMDR in your main treatment?
8. What did you think of the moment at which the EMDR treatment was given? Should EMDR be given earlier or later in the process?
9. What did you think of your EMDR therapist? What helped and what did not?
10. How would you, on a scale from 1 (terrible) to 10 (excellent), rate the therapeutic relationship between you and your therapist?
11. Are you satisfied with your choice of starting EMDR treatment? Would you make the same decision again?
12. Would you recommend EMDR therapy to others with the same complaints? Why?
13. Can you think of any improvements for our EMDR therapy?
